#### Statistical analysis

To determine if ABF intervention improves central sensorimotor integration, we will build linear regression models to simultaneously evaluate the change in CSMI measures reflecting central sensorimotor integration and the effect of ABF compared to standard of care. Our outcome will be the change in pre- versus post-rehabilitation program CSMI measures; using the change (difference) in CSMI measures will control for the correlation of the repeated pre- and post- measures within an individual as well as maximizing the number of covariates we can potentially add into the regression models. Covariates of interest are vestibular/ocular motor scores, PTSD, Veteran versus civilian status, age, and gender. In addition, we will determine whether rehabilitation improved the static and dynamic balance metrics that were measured at the pre- and post-rehabilitation testing visits.

To determine if people with CSMI impairment show sustained improvement in static and dynamic balance after rehabilitation, even after ABF is discontinued, we will use linear mixed effects regression modeling which will include a third time point of interest (6 weeks after the rehabilitation intervention has stopped). Time will be treated as a categorical variable in order to evaluate changes in CSMI scores and balance during specific time periods, in this case, between the cessation of the intervention and the 6 weeks post-intervention follow-up. We will explicitly test the significance of a group by time interaction to determine if participants in the ABF rehabilitation group showed sustained improvements in outcomes beyond that experienced by participants with the standard of care. If applicable, we will then stratify the analysis by those with abnormal/normal measures of vestibular/ocular motor function to assess the relationship between vestibular/ocular motor function deficits and sustained improvement in CSMI score and balance.

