### Participants

The study will include 65 mTBI participants and 65 control subjects for the cross-sectional arm of the study. All subjects will be between the ages of 18 and 60. Participants in the mTBI group will have a diagnosed mTBI or concussion and chronic, non-resolving complaints of balance problems determined by a score >0 on the Dizziness Handicap Inventory (DHI) at the time of testing and > 3 months post-injury. Control subjects will be gender and age matched to the mTBI group. For the second arm of the study, a subset of 40 mTBI subjects with abnormal central sensorimotor integration with or without peripheral vestibular or ocular motor deficits will be randomized into two rehabilitation groups, experimental treatment and standard of care, consisting of two rehabilitation sessions per week for 6 weeks. All subjects will be tested at either Oregon Health & Science University or the VA Portland Health Care System. All rehabilitation will take place at Oregon Health & Science University. Informed written consent will be obtained from all participants.

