#### Clinical testing for classification and covariates

To classify mTBI participants as with or without vestibular dysfunction, standard vestibular testing will be performed as described in Table 4. Clinical tests to examine potential covariates of sensory loss will also be included at the initial visit in Study 1.

**Table 4 Tab4:** List of clinical sensory and vestibular tests for classification and covariates / comorbidities of primary and secondary outcomes

Domain Tested	Test	Description	Positive Result
Sensory	Proprioception test	Assess the ability of the participant to detect the position of the great toe or ankle as it is moved by a researcher / clinician	Unable to detect changes in position
	Visual Vertical Test	Requires participant to orient a line to vertical and quantifies the deviation from vertical	Falls outside control group mean ± 2 SD
Ocular Motor	Saccadic Latency	Assesses the ability to make a rapid eye movement, latency would be the time it takes to initiate a saccade (eye movement) after the target has moved	Falls outside control group mean ± 2 SD
	Gaze	Assesses the ability to maintain stable vision on a fixed target.	
	Smooth Pursuit	Assesses the ability to accurately track/follow a moving/sinusoidal target with the eyes.	
	Convergence	Assesses the ability to view a close target without double vision	
Vestibular	cVEMP	Neurophysiological test assessing the function of the saccule	Falls outside control group mean ± 2 SD
	oVEMP	Neurophysiological test assessing the function of the utricle	
	Caloric	Assesses function of the lateral semi-circular canals and superior branch of the vestibular nerves	
	Head Impulse	Assesses function of semi-circular canals and vestibular nerve branches, specifically the lateral canals/superior vestibular nerve	

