#### Sample size

We powered the intervention study to detect improvement in the CSMI test deficit we found in our pilot subjects. Conservatively, 20 subjects will be recruited for both the experimental treatment and standard of care groups to provide results that are capable of powering a more in-depth future clinical trial investigating rehabilitation for balance deficits in mTBI patients. The CSMI test deficits observed in 3 mTBI pilot subjects and 12 healthy controls were used to power the study. Specifically, the CSMI parameter Kp under open eye surface tilting (t = -2.02, *p* = 0.065) and visual sensory weight Wvis under fixed surface visual tilting (t = 2.07, *p* = 0.060) were used to calculate sample size based on independent sample t-tests. Rehabilitation-based differences within the TBI cohort are not expected to be as extensive as those identified between mTBI subjects and controls. However, an effect size at 50% of the magnitude of the difference observed between mTBI and controls in the preliminary data (Coehn’s d = 0.748) would still yield 72% power with α = 0.10 in a repeated measures framework in as little as 10 subjects per group. Conservatively, we will recruit 20 subjects each for the experimental treatment and standard of care groups to provide results that are capable of powering a more in-depth future study investigating rehabilitation for balance deficits in mTBI patients.

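### Study 2's covariate argument for the change score does not hold, and the listed covariates leave out the pre-rehabilitation CSMI value, the adjustment most likely to sharpen the ABF comparison

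*Protocol article*

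**What the plan says.** In the protocol article, the Study 2 section on statistical analysis defines the outcome of the ABF comparison: "Our outcome will be the change in pre- versus post-rehabilitation program CSMI measures". It gives two reasons for this form. The first is that differencing "will control for the correlation of the repeated pre- and post- measures within an individual". The second is "maximizing the number of covariates we can potentially add into the regression models".

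It then names the candidates: "Covariates of interest are vestibular/ocular motor scores, PTSD, Veteran versus civilian status, age, and gender". The pre-rehabilitation CSMI value is not among them.

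The Participants section sets the size of Study 2 at "a subset of 40 mTBI subjects with abnormal central sensorimotor integration", and the Study 2 sample size section divides it: "we will recruit 20 subjects each for the experimental treatment and standard of care groups". The power statement mentions no covariates.

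**The concern.** The second reason treats the change score as a way of making room for covariates. Veteran status, age, gender, PTSD and vestibular/ocular motor results each enter as one value per person. How many such terms a model can carry depends on how many people are in it, and differencing two visits does not alter that.

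The reason matters because it supports a choice of outcome that can be less efficient than an obvious alternative. Participants enter Study 2 because their CSMI result is abnormal, so the starting value is likely to be related to the change. A change score without the baseline value as a covariate leaves that variation in the error term. With 20 people per arm, this affects the width of the interval for the randomised ABF contrast, which is also meant to inform a larger trial.

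**Working it through.** **Inputs**
- Persons: 40, 20 per arm (Participants; Study 2 sample size).
- Listed covariates: five, without baseline CSMI (Study 2 statistical analysis).
- Alpha 0.10 and d = 0.748 (Study 2 sample size). Sidedness is not stated; two-sided is used below. The sentence can be read with 0.748 as the full or the halved pilot effect; here it is taken as the standardised effect on the outcome analysed.
- Pre-post correlation rho: not given. Assumed range 0.3 to 0.7, with equal pre and post SDs.

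**The plan's own figure.** The article claims "72% power with α = 0.10 in a repeated measures framework in as little as 10 subjects per group". A within-group paired t-test (n = 10, two-sided) gives 70.5%. A baseline-adjusted between-group test (one-sided, rho 0.5) gives 72.7%. A plain two-group t-test gives 48.6% two-sided or 63.8% one-sided. So 72% is approximately reproducible under some readings. It involves no covariates, and nothing below depends on it.

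**1. Room for covariates.** Residual degrees of freedom are persons minus fitted terms.
- Change on intercept, arm and five covariates: 40 - 7 = 33.
- The same model with baseline CSMI added: 40 - 8 = 32.

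The change score therefore saves one degree of freedom.

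**2. What the omitted baseline costs.** With common SD s and no other covariates:
- Variance of change within arm: 2s²(1 - rho).
- Variance of the post value given baseline: s²(1 - rho²).
- Ratio: 2/(1 + rho). Equivalent sample size: 40(1 + rho)/2.

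| rho | Variance ratio | 40 people are worth | Ratio after the 1 df cost (x36/37) |
|---|---|---|---|
| 0.3 | 1.54 | 26 | 1.50 |
| 0.5 | 1.33 | 30 | 1.30 |
| 0.7 | 1.18 | 34 | 1.14 |

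Setting (2/(1 + rho)) x (36/37) = 1 gives rho = 72/37 - 1 = 0.946. Below about 0.95 the unadjusted change score is the less precise analysis.

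**3. What the listed covariates cost.** For k covariates unrelated to change, the expected variance of a randomised contrast is multiplied by (N - 3)/(N - 3 - k). The loss is cancelled once they explain k/(N - 3) of the variance in change.
- k = 5: 37/32 = 1.156; SE x √1.156 = 1.075, or +7.5%. Break-even R² = 5/37 = 13.5%.
- Power with no covariates: noncentrality 0.748 x √(20/2) = 2.365, 38 df, alpha 0.10 two-sided: 75.1%.
- Power with five covariates of no prognostic value: noncentrality 2.365/1.075 = 2.200, 33 df: 69.5%.
- Power if the five explain 13.5%: 74.9%. If they explain 30%: 82.4%.

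**4. Comparison.** With equal SDs, baseline CSMI alone explains 1 - (1 + rho)/2 = (1 - rho)/2 of the variance in change: 35%, 25% and 15% at rho 0.3, 0.5 and 0.7. Its break-even is 1/37 = 2.7%. The one term left off the list clears its threshold easily across this range. Whether the five listed terms clear theirs is unknown.

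**The case against.** The sentence can be read as describing capacity rather than a commitment: it says what could be added, and it is the second of two reasons. The first reason is sound as far as it goes, since one difference per person leaves no within-person correlation to model. Randomisation keeps the change-score contrast unbiased. Study 2 is described as a pilot, and a separate mixed model with a group-by-time test is planned. An analysis plan that is not shown may fix the covariates and may include baseline.

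Much of this stands, and it rules out three stronger readings that a reader might infer.
- *Covariate adjustment makes the ABF comparison less precise than the unadjusted one.* The document gives no R². Above 13.5% for five terms, adjustment gains precision.
- *All eight ocular motor and vestibular tests in Table 4 will enter as separate terms.* The plural wording leaves the form open, but the article elsewhere classes vestibular/ocular motor function as normal or abnormal. Five terms is the reading taken here.
- *The result will be picked from many possible models.* Nothing in the article suggests this, and an article commonly leaves the final covariate set to the analysis plan.

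The objection does not rescue the stated reason. A baseline-adjusted regression also has one row per person, so it meets the first reason equally well, and the second reason is worth one degree of freedom.

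**Conclusion.** The point holds as a correctable weakness in a stated choice, not as a source of bias. The covariate argument for the change score is wrong, because at most 40 persons set the limit and the saving is one degree of freedom. Omitting baseline CSMI multiplies the variance by 1.54, 1.33 or 1.18 at rho 0.3, 0.5 or 0.7, so that 40 people do the work of about 26, 30 or 34.

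These sizes rest on an assumed correlation, equal pre and post SDs and no other covariates. With unequal SDs and L = SD(pre)/SD(post), the ratio becomes 1 + (L - rho)²/(1 - rho²). This is never below 1, so apart from the one degree of freedom the change score cannot gain, though the size of the loss would differ.

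The cost of the five listed covariates is conditional: at most an average SE increase of 7.5% (power 75.1% to 69.5%), and a gain instead if they explain more than about 13.5% of the variance in change.

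**What to change.** In the Study 2 statistical analysis:
- Delete the covariate-maximising reason for the change score.
- Make the primary ABF comparison a regression of post-rehabilitation CSMI on arm and pre-rehabilitation CSMI. Change may be kept as the outcome if preferred: with baseline in the model, the arm estimate and its SE are identical.
- Keep any other listed covariates few, chosen for expected prognostic value and prespecified.
- Label further adjusted models as sensitivity analyses.

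The cost is one degree of freedom and a few lines of analysis text. The baseline value is already collected, and sample size, visits and procedures do not change.

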## Methods / Design

This study has two parts: Study 1) A cross-sectional study to identify and characterize balance control strategies after mTBI compared to healthy controls, and Study 2) An interventional randomized pilot study using a novel ABF rehabilitation technique to improve central sensorimotor integration after mTBI. All subjects will complete baseline clinical sensory, ocular motor, vestibular, neurocognitive, static and dynamic balance, and central sensorimotor integration testing. Following baseline testing, a subset of mTBI participants will be randomized into two treatment groups for 6 weeks of rehabilitation. Within 1 week after completing the rehabilitation program, subjects will repeat the balance and central sensorimotor integration testing to examine the short-term effects of rehabilitation. Subjects will complete the balance and central sensorimotor integration testing a third time, 6 weeks after completion of the rehabilitation, to assess retention. This trial is registered at clinicaltrials.gov (NCT02748109).

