### Study 2: Rehabilitation of balance deficit

#### Assessment procedures

Subjects with mTBI who participate in Study 1 will be screened for Study 2. An investigator will verbally explain the consent form and time commitments involved with the rehabilitation, allow the person ample time to read through the consent form and then will acknowledge consent by signing the form. For Study 2, 40 mTBI participants will participate in a 6-week rehabilitation program randomized to either 1) a standard vestibular focused rehabilitation program or 2) the same standard vestibular focused rehabilitation program with the addition of audio biofeedback. Post-rehabilitation assessments will be conducted one week after the conclusion of the program. Retention will be assessed 6 weeks following the post-rehabilitation session. A flowchart illustrating the study design is depicted in Fig. 3.

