#### Primary and secondary outcome measures

The primary outcome measure is the change between pre-rehabilitation, post-rehabilitation, and 6-week follow-up testing of the model-based parameters of the novel CSMI test (Table 2). Secondary outcome measures are the changes between pre-rehabilitation, post-rehabilitation, and 6-week follow up testing of the clinical and objective balance measures described in Study 1 and in Table 3. Additional secondary outcome measures from the at-home inertial sensors will include activity rate and average turning speed and number of turns.

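### Study 2's group-by-time test, over the period the plan names, does not test a sustained ABF benefit; the group contrast from pre-rehabilitation to 6 weeks should be named instead

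*Protocol article*

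**What the plan says.** In the protocol article's Statistical analysis section for Study 2, two analyses bear on ABF.

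- **Pre to post.** A linear regression on change scores compares the arms: "Our outcome will be the change in pre- versus post-rehabilitation program CSMI measures". It stops at the post-rehabilitation visit.
- **Retention.** The article plans "linear mixed effects regression modeling which will include a third time point of interest", the third point being the 6-week visit. On the coding of time it says "Time will be treated as a categorical variable in order to evaluate changes in CSMI scores and balance during specific time periods", and it specifies the period as "in this case, between the cessation of the intervention and the 6 weeks post-intervention follow-up". The next sentence gives the test: "We will explicitly test the significance of a group by time interaction to determine if participants in the ABF rehabilitation group showed sustained improvements". That sentence goes on to make standard of care the comparator.

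The section on primary and secondary outcome measures defines the Study 2 primary outcome as the "change between pre-rehabilitation, post-rehabilitation, and 6-week follow-up testing of the model-based parameters of the novel CSMI test". It does not say which pair of visits carries the comparison.

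The follow-up visit is dated in two ways. Methods / Design puts it "6 weeks after completion of the rehabilitation, to assess retention", and the Statistical analysis section also counts from the end of the intervention. Assessment procedures for Study 2 says "Retention will be assessed 6 weeks following the post-rehabilitation session", and places that session one week after the programme ends.

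**The concern.** Sustained improvement beyond standard of care has a definite meaning in this design: the ABF-minus-standard difference in change from pre-rehabilitation is still present at 6 weeks. That comparison has to be anchored at baseline. The period the plan names starts at the end of treatment, after any ABF advantage has already arisen, so the advantage cancels out of the change being compared. The other way to read a group-by-time interaction with three categorical visits is the overall 2-df test. That test asks only whether the arms' profiles differ in shape, not whether a difference lasted.

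The Discussion intends to conclude that maintained improvement after the device is withdrawn reflects recalibration and not sensory substitution. Loss of the advantage once feedback stops is the pattern substitution would predict, so the between-arm test should be able to tell retention from loss.

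**Working it through.** **The plan's own figure.** No power is stated for the retention test. The only figure for Study 2 is 72% power with 10 per group, d = 0.748 and alpha 0.10 in a repeated measures framework. With those inputs a two-sided two-sample t test gives 48.6% and a paired t test in one group of 10 gives 70.5%. A two-sided test on change scores gives 66.7% at correlation 0.70 and 73.6% at 0.75. So 72% is attainable, but the article does not give the test, sidedness or correlation needed to reproduce it. Nothing below depends on it.

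**Inputs.** 20 per arm (Sample size, Study 2). ABF-minus-standard difference at post d = 0.75 SD (the article's 0.748, rounded; applying it here is my choice). Assumed: SD 1 at each visit, equal correlation ρ between visits of 0.3, 0.5 or 0.7, no dropout, no covariates, two-sided alpha 0.05. The article states no alpha for this test.

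**Patterns.** Group differences at pre, post and follow-up are (0, d, d) for full retention and (0, d, 0) for complete loss.

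**Reading 1: interaction over post to follow-up.** The quantity tested is the follow-up difference minus the post difference.

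- Full retention: d − d = 0 for any d and any ρ. Rejection is at alpha, the same as with no ABF effect at all.
- Complete loss: 0 − d = −d. The test has power, but the sign shows ABF losing ground.

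**Reading 2: overall interaction, 2 df.** The noncentrality is λ = (n/2) × Σ(δ_j − mean δ)² / (1 − ρ), with 2 and 76 df.

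- Full retention: mean 2d/3, sum of squares (4 + 1 + 1)d²/9 = 2d²/3.
- Complete loss: mean d/3, sum of squares (1 + 4 + 1)d²/9 = 2d²/3.

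The two are identical. With d = 0.75, 2d²/3 = 0.375, so λ = 10 × 0.375/(1 − ρ) = 5.36, 7.50 and 12.50.

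**Baseline-anchored contrast: pre to follow-up, 1 df.** SE = √(2 × 2(1 − ρ)/20) = 0.374, 0.316 and 0.245. The noncentrality is 0.75/SE = 2.00, 2.37 and 3.06 on 38 df.

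| Proportion significant, alpha 0.05 | ρ = 0.3 | ρ = 0.5 | ρ = 0.7 |
|---|---|---|---|
| Post to follow-up, full retention | 5% | 5% | 5% |
| Post to follow-up, complete loss (negative sign) | 50% | 64% | 85% |
| Overall 2 df, full retention | 52% | 67% | 88% |
| Overall 2 df, complete loss | 52% | 67% | 88% |
| Pre to follow-up, full retention | 50% | 64% | 85% |
| Pre to follow-up, complete loss | 5% | 5% | 5% |

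Simulation with 20,000 trials per scenario and d = 0.748 agrees to within about a percentage point. At alpha 0.10, the level in the sample-size text, and ρ = 0.5, the simulated rates are 77% (overall, full retention), 78% (overall, complete loss), 74% (pre to follow-up, full retention) and 10% (post to follow-up, full retention).

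**Visit date.** Six weeks from the end of rehabilitation is week 6. Six weeks from a session held one week after the end is 1 + 6 = week 7.

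**The case against.** The strongest reply is that the article does not settle on either test. It names no 2-df test, and the sentence on the interaction does not itself repeat the period. The model includes the pre-rehabilitation visit and the primary outcome spans all three visits, so the group-by-follow-up term against baseline is already available. Choosing a coefficient is commonly left to an analysis plan, which is not shown here. Further, hypothesis (c) in the Background concerns sustained improvement after rehabilitation with ABF and is not itself a comparison between arms. Post-to-follow-up change is a fair look at maintenance, and it complements the pre-to-post regression.

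Much of this stands. The right contrast is available at no cost, and post-to-follow-up change is a legitimate estimate of decay. It does not remove the point. The article states a between-arm question, a test and a period, and the period does not match the question. Nor does a non-significant decline establish retention.

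Two stronger readings are tempting and should be resisted. A reader might infer that one and the same test both misses full retention and passes off a lost benefit as sustained. The failures belong to different readings: over the named period a lost benefit has a negative sign and misleads only if the sign is ignored, and under the overall test full retention is not null. A reader might also infer that the overall interaction is significant whenever the arms differ at some visit. A constant difference at all three visits gives no interaction, and otherwise significance is a matter of power.

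**Conclusion.** The concern holds in this form: the stated test and period do not answer whether ABF gave sustained improvement beyond standard of care. Over the named period, full retention gives a null result by construction, whatever the effect size or correlation. Under the overall interaction, full retention and complete loss are indistinguishable by significance, at about 52%, 67% and 88% each for ρ = 0.3, 0.5 and 0.7. That equality relies on equal correlations between visits; the percentages also rely on 20 per arm, 0.75 SD, alpha 0.05 and no dropout.

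The documents do not support saying that the trial cannot answer the question, since the planned model holds the data needed. Nor should the pre-to-follow-up contrast be presented as well powered: 85% is the favourable end of a range that starts at 50%. The mismatch in the follow-up date is real but minor, and the argument about the contrast does not rest on it.

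**What to change.** 1. In the same mixed model, name the test of sustained ABF benefit as the 1-df ABF-minus-standard difference in change from pre-rehabilitation to the 6-week follow-up.
2. Report post-to-follow-up change in each arm, and its difference between arms, with 95% confidence intervals as the estimate of decay. State that a non-significant decline will not be read as proof of retention.
3. If an overall interaction is reported as well, say that its significance is not evidence of a sustained effect.
4. Reconcile the date of the follow-up visit across Methods / Design, Assessment procedures for Study 2 and Statistical analysis for Study 2.

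The cost is wording only. The model, data and sample size do not change, and no visit is added.

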If a portion of subjects with chronic balance problems after mTBI have abnormal CSMI test measures but normal clinical vestibular testing results, this suggests that sensory integration processes in the brain can be impaired following mTBI, even without peripheral sensory deficits, and that abnormal central sensorimotor integration plays a key role in persistent abnormal balance in subjects with normal vestibular function. If a portion of mTBI subjects have abnormal CSMI test measures and abnormal clinical vestibular function, the key mediator for balance problems is less clear and may be due to the peripheral vestibular dysfunction, abnormal central sensorimotor integration, or inadequate adaptation of central sensorimotor integration to account for abnormal sensory information. If we find that abnormal central sensorimotor integration mediates abnormal static or dynamic balance, rehabilitation will need to be focused on improving central sensorimotor integration to improve balance. If we find that CSMI scores improve with rehabilitation, we will conclude that central sensorimotor integration strategies are flexible and can improve with training. Further, if we find that central sensorimotor integration and gait and balance jointly improve with rehabilitation, we will have further evidence that central sensorimotor integration plays a key role in the mediation of gait and balance following mTBI. If we find a greater improvement in the ABF group, we will conclude that ABF may facilitate improved rehabilitation. Finally, if we find that people with central sensorimotor integration impairment maintain improvements after stopping the use of ABF device, we will conclude that a recalibration of sensory integration and/or sensorimotor transformation for balance has occurred, rather than sensory substitution that requires active ABF. If we find that sensory strategies can change with practice and biofeedback, we will conclude that this targeted approach to balance rehabilitation should be explored further in a larger, randomized trial. It is possible that different subclasses based on CSMI measures respond differently to rehabilitation or ABF-augmented rehabilitation. In such a case, the results of this study will provide valuable information for powering an in-depth future study carefully examining the relationship between CSMI subclasses and the response to rehabilitation with and without ABF. The results of this study will further our understanding of the mechanisms underlying posture and gait dysfunction in individuals with chronic mTBI and inform future studies about the efficacy of ABF augmented rehabilitation programs.

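### Stratifying Study 2 by vestibular/ocular motor status does not compare the strata; a status interaction in the mixed model already planned would (minor)

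*Protocol article*

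**What the plan says.** The Study 2 statistical analysis section of the Protocol article plans a linear mixed model over three visits: before rehabilitation, after it, and 6 weeks later. On time it says "Time will be treated as a categorical variable", and on the comparison of arms "We will explicitly test the significance of a group by time interaction". A last, conditional step follows: "we will then stratify the analysis by those with abnormal/normal measures of vestibular/ocular motor function", with the purpose "to assess the relationship between vestibular/ocular motor function deficits and sustained improvement in CSMI score and balance".

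Elsewhere in that section vestibular/ocular motor status appears only in the separate model for pre-to-post change: "Covariates of interest are vestibular/ocular motor scores, PTSD, Veteran versus civilian status, age, and gender". No interaction with this status is named in either model.

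The Participants section admits people both with and without these deficits to Study 2 but does not give the expected split. On size, the Study 2 sample size section says "we will recruit 20 subjects each for the experimental treatment and standard of care groups". It adds that the results should be able to power a later, more detailed trial.

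**The concern.** Whether a deficit changes the amount of sustained improvement is a question about the difference between two estimates. Running the analysis once in each stratum gives the two estimates but not their difference or its uncertainty. The analysis being stratified is built around a significance test, so the natural output is one p-value per stratum. The natural misreading is that benefit in one stratum and none in the other means the strata respond differently. With 40 people divided into four cells, that pattern occurs often when the true effects are equal.

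The data are meant to help power a later trial. A difference between strata that is only noise could be carried into that trial's assumptions. The plan already avoids the same error for treatment, where it tests group by time and does not test time separately within each arm.

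**Working it through.** **Inputs from the Study 2 sample size section.** 20 per arm; "Coehn’s d = 0.748", read as the halved pilot effect; alpha 0.10; 72% power with 10 per group in a repeated measures setting.

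**Assumptions.** The section does not say whether the test is one- or two-sided, so two-sided testing is assumed. The stratum split is not given; I use 10/10 per arm and vary it to 14/6 per arm (28 and 12 people in all). Alpha 0.05 is shown as well, because the Study 2 analysis section gives no level.

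**Step 1: the plan's own 72%.** By noncentral t with 10 per group, d = 0.748 and two-sided alpha 0.10:
- paired test within one group: 70.5%, close to 72%;
- two-arm comparison of change scores: 72% if the pre/post correlation is about 0.74, a value the article does not give;
- independent two-arm t-test with no repeated-measures gain: 48.6% (35.4% at alpha 0.05).

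Ten per group is also the size of each stratum under an even split, so 48.6% and 72% serve as a low and a high value for stratum power.

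**Step 2: chance that exactly one stratum is significant when the true benefit is equal.** With stratum powers p1 and p2, this is p1(1 - p2) + p2(1 - p1).

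| Case | p1, p2 | Exactly one significant |
|---|---|---|
| alpha 0.10, even, independent t | 0.486, 0.486 | 2 x 0.486 x 0.514 = 50% |
| alpha 0.10, even, plan's 72% | 0.72, 0.72 | 2 x 0.72 x 0.28 = 40% |
| alpha 0.10, 14/6, independent t | 0.611, 0.333 | 0.611 x 0.667 + 0.333 x 0.389 = 54% |
| alpha 0.10, 14/6, variance matched to 72% | 0.847, 0.511 | 0.847 x 0.489 + 0.511 x 0.153 = 49% |
| alpha 0.05, even, independent t | 0.354, 0.354 | 2 x 0.354 x 0.646 = 46% |
| alpha 0.05, 14/6, independent t | 0.478, 0.217 | 0.478 x 0.783 + 0.217 x 0.522 = 49% |
| alpha 0.10, even, d = 0.374, independent t | 0.208, 0.208 | 2 x 0.208 x 0.792 = 33% |
| alpha 0.10, no benefit | 0.10, 0.10 | 2 x 0.10 x 0.90 = 18% |
| alpha 0.05, no benefit | 0.05, 0.05 | 2 x 0.05 x 0.95 = 9.5% |

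With the variance matched to 72% power, the alpha 0.05 figures are 48% (even) and 57% (14/6). The d = 0.374 row applies if 0.748 is the effect before halving. If stratification follows only a significant overall result, which the conditional wording may mean, the rate at alpha 0.10 with d = 0.748 is 41-64% (simulation, 50,000 runs per case).

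**Step 3: a direct comparison.** In the same simulations, a treatment-by-status interaction test on the change score was falsely positive in 9.8-10.3% of trials at alpha 0.10 and about 5% at alpha 0.05, whatever the common effect.

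**Step 4: its precision.** With 10 per cell, the standard error of the between-stratum difference is sqrt(4/10) = 0.63 SD. The difference detectable at 80% power and two-sided alpha 0.05 is about (1.96 + 0.84) x 0.63 = 1.8 SD. A true difference between strata of 0.748 would be detected 29-48% of the time at alpha 0.10 and 18-36% at alpha 0.05.

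**The case against.** The strongest reply is that the decision rule is inferred. A reader might take the article to say that significance in one stratum only will count as a difference. It does not say so, and reporting stratum estimates with intervals would fit the same sentence. This stands, so the rates above are conditional on that reading. It does not remove the mismatch, because side-by-side estimates still leave the difference unestimated.

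A reader might also infer that a false difference appears about half the time in general. It does not. With equal strata one half is the maximum, reached at stratum power near 50%. The plan's own 72% gives 40%, and no benefit gives 18% or 9.5%. The last two figures matter because the section singles out the interval from the end of treatment to follow-up. If both arms merely hold their gains, the group difference in change over that interval is near zero.

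The Discussion remark "It is possible that different subclasses based on CSMI measures respond differently to rehabilitation or ABF-augmented rehabilitation" might be taken as showing that these strata will steer the next study. It concerns subclasses by CSMI measures, which is a different classification. Study 2 participants all have abnormal CSMI and differ in vestibular/ocular motor status. Only the general aim of powering a later trial, in the sample size section, is relevant.

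The covariate in the change model can show how pre-to-post change varies with status, averaged over arms. It covers neither the 6-week outcome nor a difference in the ABF effect.

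Finally, a single interaction term does not settle the question. With time categorical over three visits, status x group x time has 2 degrees of freedom unless one contrast is named, and its power is low. Both limits are accepted in the fix.

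**Conclusion.** The concern holds in limited form. The method named does not compare the strata, which is what its stated purpose needs. If significance is compared across strata, a spurious difference is expected in about 40-54% of trials at alpha 0.10 with an equal benefit of d = 0.748, and in 46-49% at alpha 0.05 by independent t-test. It falls to about 33% at alpha 0.10 if d is 0.374, and to 18% or 9.5% with no benefit. Even these lower rates exceed the error rate of an interaction test at the same alpha.

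The figures rest on an assumed split of 10/10 to 14/6 per arm, two-sided tests, and a reading rule the article does not state. Severity is minor: the step is conditional and secondary, Study 2 is described as a pilot, and neither the primary change model nor the group-by-time test is affected.

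**What to change.** In the Study 2 statistical analysis section, replace the separate stratified analyses with the planned mixed model on all 40 participants, adding vestibular/ocular motor status and its interactions. Name the contrast in advance:
- if the question is whether the ABF effect depends on status, use status x group x time for one stated time contrast;
- if it is whether improvement depends on status regardless of arm, use status x time.

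Report the between-stratum difference with its confidence interval, take the stratum estimates from the same model, label the analysis exploratory, and give no separate stratum p-values.

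The cost is a sentence or two of text, with no new data or participants. The downside is a visibly wide interval: with a standard error of 0.63 SD under an even split, a 95% interval extends about 1.96 x 0.63 = 1.2 SD either side. That imprecision is already present in the stratified version, where it is hidden.
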